### Trial research-related outcomes

#### Primary worker measures (at baseline, 2 months and 4 months)

The primary research outcome of the intervention will be assessed monthly, after randomisation at the worksite level using 1:1 ratio approach. For the primary research outcome, we will contact (text message) the workers from the control and intervention group on monthly basis and will ask them to report if they are still on sick leave or if they are planning to RTW. For those who have returned to work, we will ask them for the date of their first day back at work (and whether it is a partial or full return). The RTW date will also be collected from the organisational records. Secondary outcome measures of the intervention will be assessed at 3 timepoints (within 2 weeks of consenting, at 2 months and at 4 months).

Number of days of sick leave will be recorded from the employer and from the worker (self-report). Self-report data will be collected at baseline at 2 months and at 4 months (from control and intervention participants) using an online survey. Participants will be asked the following questions: (a) are you still on sick leave? If yes, do you have an RTW date? If not on sick leave, when did you go back to work? (b) How many hours are you currently working? (c) Is this the same as before your sick leave? Those who have returned to work will be asked to report their first day back at work (and whether it is a partial or full return). The last data collected will be at 4-month post-randomisation.

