## Background

In Britain, mental health issues increasingly account for a significant proportion of long-term sickness absence from work [1], and those who are absent for 6 months or longer have less than a 50% chance of ever returning to employment [2]. Sickness absence associated with poor mental health costs UK employers £7 billion each year [1], and a recent report by the Office for National Statistics (2019) [3] suggests sickness absence due to poor mental health is on the rise (12.4% in 2018 compared to 9.1% in 2009). The cost of sickness absence is not at an economic level only, as there are major social, psychological and financial implications for individuals on sick leave and for those unable to RTW [4]. These include inactivity, isolation, reduced workability and productivity [5–8], with reduced wellbeing and impaired self-image leading to the individual potentially withdrawing from society and support networks [5]. Long-sickness absence is also a predictor of disability pension, higher risk of unemployment and job termination [9]. Therefore, early intervention to support a worker’s RTW is not only cost-effective for the employer (e.g. in terms of reduced turnover, recruitment costs, retention of knowledge) but also is vital for workers’ health and wellbeing.

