#### Outcome measures

Primary and secondary outcome measures will be collected at baseline, 2 months and 4 months. Outcome measures will be collected for both workers and managers. Outcome measures have been grouped as process outcomes and research outcome measures (see below), and they will be collected using Qualtrics; data and personal details will be stored according to the General Data Protection Regulation (GDPR, 2016/679) and research governance guidelines. A summary of the outcome measures at the various time points is provided in Table 3. Qualitative interview data will be collected either over the phone or using online conferencing facilities. Both full-return (defined for this study as working the same days or hours per week as before sickness absence in an identical or equivalent role for at least 4 weeks) and partial RTW (defined as working any number of hours in any role) data will be collected via text messages.

**Table 3 Tab3:** Schedule of process and research outcome measures

Measured outcome	Assessment tool	Pre-randomisation	Baseline	Month 1	Month 2	Month 3	Month 4
Process outcomes							
Long-term sickness absence data for the past 12 months	Reports review	**X**					
Frameworks (sickness absence policy, return-to-work policy, mental health training and support)	Policy review	**X**					
Number of workers on (a) sick leave (≥ 8 days) and their reasons and (b) that employers have contacted to take part in the study (until the end of the study)	Checklist		**X**	**X**	**X**	**X**	**X**
Number of persons responsible for managing the sick leave and return to work (a) consenting to take part and (b) attending the training	Checklist	**X**					
Toolkit use	Volute records and interview		**X**				**X**
Feasibility and acceptability of intervention	Interview						**X**
Toolkit use	Interview						**X**
Research outcome worker							
Workers sick leave	Self-reported number of days						**x**
Depression	Patient Health Questionnaire- 9		**X**		**X**		**X**
Anxiety	General Anxiety Disorder-7		**X**		**X**		**X**
Sick leave duration	Number of days on sick leave		**X**		**X**		**X**
Self-efficacy to RTW	11-item Return-to-work Self-Efficacy Scale		**X**		**X**		**X**
Readiness to RTW	13-item Readiness to Return to work		**X**		**X**		**X**
Readiness to stay at work	9-item Readiness to Stay at Work Scale		**X**		**X**		**X**
Workplace communication	6-item Workplace Health Communication Scale		**X**		**X**		**X**

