### Statistical data analysis

This study will be analysed according to the Consolidation Standards of Reporting Trials (CONSORT) statement for cluster RCTs [49]. As this is a feasibility study, main analysis will include descriptive statistics (mean, SDs and medians). Data will be analysed using IBM SPSS statistics. Data analysis will be performed after the last trial participant has completed their 4-month post-intervention. A baseline table (descriptive statistics and frequencies) will compare the demographic and clinical characteristics including gender, age, education, number of days on sick leave, mental health status, readiness, intention and self-efficacy to RTW, work support, communication, performance at work, sleep and physical activity, between the 2 arms. As this is a pilot trial, no emphasis will be put on the *p*-values, as the main purpose of the analysis is to calculate confidence intervals (CI). Statistical analysis will be carried out on an intention to treat basis with missing outcome data being imputed using multiple imputation. To explore the extent and patterns of missing outcome data, we will report the proportion of missing values per item, proportion of participants who complete all items on the questionnaire and the proportion of respondents who answer at least 50% of the items in a scale. The proportion of missing data will also be reported for the other key outcomes and compared between the participants from intervention and control practices. The point estimate of the proportion and its 95% confidence interval (CI) will be provided for the primary research outcome, i.e. number of days taken to RTW (partial or full) for the intervention and the control arms. Key baseline characteristic will be compared between those participants followed up and those lost to follow-up at each timepoint.

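### The primary-outcome questions have no answer for a worker whose sick leave ended because the job ended, and the imputation rule makes no exception for such workers

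*Protocol article*

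**What the plan says.** The primary research outcome is the number of days until part-time or full-time RTW (Objectives; Statistical data analysis). It has two self-report sources, both described under Primary worker measures:

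- **Monthly text.** The team "will ask them to report if they are still on sick leave or if they are planning to RTW". Those already back are asked for their first day and whether the return is partial or full.
- **Survey at baseline, 2 and 4 months.** Workers are asked whether they are still on sick leave. If they are, they are asked whether they have a return date. If they are not, the item reads "If not on sick leave, when did you go back to work". A further item asks "How many hours are you currently working".

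The same section adds an employer source: "The RTW date will also be collected from the organisational records".

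Outcome measures gives the definition "partial RTW (defined as working any number of hours in any role". Full return, by contrast, is tied to the former hours and to the same or a comparable role for at least 4 weeks.

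Statistical data analysis specifies intention to treat with "missing outcome data being imputed using multiple imputation", and states no exception.

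The Background says: "Long-sickness absence is also a predictor of disability pension, higher risk of unemployment and job termination".

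**The concern.** The survey item treats being off sick leave as being back at work. These differ for a worker who resigned, was dismissed, or left on a disability pension. The Background lists job termination, unemployment and disability pension as risks of long absence, so the study has reason to expect some such workers, yet the outcome questions give them no category.

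The primary outcome pools partial and full return, so any role that qualifies as partial return ends the count of days. The imputation rule fills in whatever is left blank.

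Three uses of the data are exposed. The pilot mean and SD are to feed the main trial's sample size (Process outcomes). Productivity costs are calculated from the days taken to RTW (Cost analysis). And the study aims at a sustainable return, for which losing the job is a plain failure that the outcome cannot currently show.

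**Working it through.** The plan has no figure of its own to reproduce here. The first step follows a leaver through the printed rules. The second gives a scale under stated assumptions.

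**Step 1. What the rules allow for a worker whose employment ended**

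| What the worker does | Rule that applies | Possible result |
|---|---|---|
| Gives the day sick leave ended | Survey item for those not on sick leave | An exit is dated as a return |
| Gives the start date of a job elsewhere | Partial RTW covers any role; no employer is specified | May count as partial RTW |
| Leaves the date blank | Multiple imputation, no stated exception | A return date is imputed for a return that did not occur |

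Other items could expose a leaver, but none is tied to days to RTW:

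- Employer records would hold no return date, but the article does not say which source prevails or how a missing employer date is read.
- The hours item could show zero hours, but not for someone working elsewhere.
- Self-reported employment status is named only in the Cost analysis.
- Withdrawals and their reasons (Process outcomes) concern leaving the study, not leaving the job.

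**Step 2. Size, as an illustration**

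Input from the documents: 30 participants per arm, workers and managers together (Sample size), and follow-up to 4 months after randomisation, taken as 122 days.

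Assumptions, because the documents give no figures: n = 15 to 30 workers per arm; share leaving within 4 months s = 2% to 10%; exit on day d = 30 to 90; a worker not returned by the end of follow-up is counted at 122 days; SD of days to RTW 30 to 45.

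*Expected leavers per arm* = n × s
- Lowest: 15 × 0.02 = 0.3
- Highest: 30 × 0.10 = 3.0

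*Chance of at least one leaver in an arm* = 1 − (1 − s)^n
- Lowest: 1 − 0.98^15 = 0.26
- Highest: 1 − 0.90^30 = 0.96

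*Fall in an arm's mean if every exit is recorded as a return* = s × (122 − d)

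| s | d = 30 | d = 60 | d = 90 |
|---|---|---|---|
| 2% | 1.8 | 1.2 | 0.6 |
| 5% | 4.6 | 3.1 | 1.6 |
| 10% | 9.2 | 6.2 | 3.2 |

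*Sampling error for comparison*: 95% half-width of an arm mean = 1.96 × SD / √n, ignoring clustering
- Smallest: 1.96 × 30 / √30 = 10.7 days
- Largest: 1.96 × 45 / √15 = 22.8 days

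*Shift in the difference between arms* = the shift in one arm minus the shift in the other. With equal leaving and equal exit days it is zero. With 10% leaving in one arm and 2% in the other, all on day 30, it is 9.2 − 1.8 = 7.4 days.

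These figures cover only exits recorded as returns. For imputed dates, neither size nor direction can be derived, because the imputation model is not described.

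**The case against.** The strongest reply is that this is a condensed article. Full response options, coding of leavers and exceptions to imputation normally sit in the questionnaire, full protocol or analysis plan. That is fair for what the article leaves unsaid. Here, however, it prints the outcome question and states the imputation rule, and followed as printed these mishandle a leaver.

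Second, a job loss would probably be noticed. Numbers are small, the HR contact is met monthly, employers supply RTW dates, hours are asked, and workers are interviewed at 4 months. This stands as far as it goes: exits are not invisible. But noticing an exit does not settle how it enters days to RTW.

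Third, the wording on any role most naturally means modified duties, and counting work elsewhere as RTW is a legitimate outcome choice. Both points stand. The need is to state the choice; confining RTW to the same employer is not something the documents require.

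Fourth, the stakes are limited. Reach, uptake and completion are the primary feasibility endpoints, the analysis is mainly descriptive, and p-values get no emphasis. This stands, and limits the harm to the pilot estimates and costs.

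A reader might go further and infer that leavers will receive false return dates. The documents do not support this: the text asks for a date only from those already back, and a leaver may leave the survey item blank or explain. Nor does the Background say that long absence causes job loss; it speaks of prediction and risk. Its figure of under 50% ever returning concerns absences of 6 months or longer, whereas workers enter at 8 to 50 days and are followed for about 122 more, reaching roughly 130 to 172 days.

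**Conclusion.** The point holds as a defect in a printed instrument and a stated rule. A worker whose employment ended has no valid answer to the outcome question, and the plan's rules allow that worker to be dated as returned, counted as a partial return through other work, or given an imputed return.

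The size is uncertain and probably modest. Under the assumed 2–10% leaving and exit on day 30–90, an arm's mean would move by about 0.6–9 days, which is below the illustrative half-width of about 11–23 days for that mean. Even so, at the upper end of the assumptions at least one leaver per arm is likely, and systematic misclassification does not shrink with more participants as sampling error does. The SD passed to the main trial would also be affected, by an amount that cannot be derived from the documents.

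Two stronger conclusions are tempting and should not be drawn. One is that the primary-outcome estimates are biased towards faster return. That direction follows only for exits recorded as returns; for imputed leavers it is not shown. The other is to read the shift as a fraction of the 15–30 day reduction cited in the Background. That figure is an effect of intervention, whereas the shift applies to one arm's mean and carries over to the comparison only if leaving, or its timing, differs by arm.

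**What to change.** 1. Add a response to the monthly text and to the 2- and 4-month surveys: *no longer employed by this organisation (date, reason)*. Confirm it at the monthly HR contact already planned.
2. In the outcome definition, state whether work for another employer counts as RTW.
3. Report leavers by arm as a separate end state, treated as a competing event for return.
4. State that no return date is imputed for a worker known to have left employment.

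The cost is one extra response option, one question at an existing meeting, a line in the outcome definition and slightly more analysis. No extra visits are needed. The number leaving in each arm would itself be useful for planning the main trial.

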**Methods and design:**

A two-arm feasibility RCT with a 4-month intervention will be conducted in SMEs and LE enterprises from the Midlands region, UK. At least 8 organisations (4 controls and interventions), and at least 60 workers and/or managers, will be recruited and randomised into the intervention and control group (30 interventions, 30 controls). Workers on long-term sickness absence (LTSA) (between 8 and 50 days) and managers with a worker on LTSA will be eligible to participate. The intervention is a behavioural change programme, including a managers and workers RTW toolkit, focused on supporting sickness absence and RTW through the provision of knowledge, problem-solving, action planning, goal setting and positive communication that leads to a sustainable RTW. Organisations assigned to the control group will continue with their usual practice. Measurements of mental health, RTW, work outcomes, quality-of-life, workplace support and communication and other demographic data will be taken at baseline, 2 months and 4 months. Feasibility will be assessed based on recruitment, retention, attrition, completion of measures and intervention compliance for which specific process and research outcomes have been established. A process evaluation will explore the experiences and acceptability of the intervention components and evaluation measures. Exploratory economic evaluation will be conducted to further inform a definitive trial.

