## Methods/design

### Study design

This is a feasibility randomised controlled trial with a 4-month intervention (called PROWORK) to be delivered to employees and managers in SMEs and LEs. Each of the organisations are the units of randomisation (the clusters), with data collected from individual workers (the participants). In addition, managers with a worker on LTSA will be eligible to participate. Although dyads of managers and workers can participate, this is not essential. This design overcomes the problem of contamination between the intervention and control arms and the problems associated with individually consenting and randomising workers to a trial where the employers may be managing the sick leave of 2 or more workers. A repeated measures design will be adopted, whereby worker participants will complete outcome measures at baseline, 2 months and 4 months, and managers will complete outcome measures at baseline and 4 months. Each organisation’s involvement in the trial is for 12 months. Observations and end-of-study interviews with workers and managers and informal monthly meetings with the organisation’s human resources representative will be conducted throughout the intervention period as part of a full process evaluation. Figure 1 shows the study flow diagram, and Table 1 indicates the schedule of enrolment, intervention and outcome measures. The project has been granted ethical approval by the Loughborough University Ethical Advisory Committee (reference 2020-1889-2041). The trial was preregistered in the ISRCTN registry on 15th December 2020 (10.1186/ISRCTN90032009).

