#### Participant recruitment, inclusion criteria and consent

Within participating organisations, workers (over 18 years of age) that go on sick leave for at least 8 days (or from issue of fit note) and up to 8 weeks (50 days) and/or the person managing their sickness absence are eligible to participate. Sickness absence must be associated with either poor mental wellbeing or where poor mental wellbeing may be a comorbidity [14]. Once the worker on long-term sick leave is identified by the organisation, both the worker, and their manager, will be sent a detailed information sheet about the study so that they can make an informed decision about their participation. Those interested in taking part will contact the research team directly either by phone or email, at which stage they will be consented by the research team.

Workers on long-term sick leave will not be eligible to participate in PROWORK if they are on sick leave (a) with a psychotic episode such as schizophrenia, or with substance abuse, (b) whilst under formal investigation for misconduct or in the formal process of disciplinary action, (c) due to cancer and signed off work for at least 6 months and (d) due to a neurological condition (e.g. multiple sclerosis, Parkinson, dementia).

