### Workers

Workers on sick leave will receive the intervention until RTW or 4 months (last follow-up) from when the worker has completed baseline measures. PROWORK includes a step-by-step action-oriented toolkit that provides guidance and support from initial absence to post RTW. Three workplace coaching sessions based on goal setting and problem-solving will be offered to worker by a trained project researcher over the phone. These will be delivered at three timepoints throughout the intervention: (1) at the start, to support making contact, to coach the participant in the use of the resources, to build a relationship with the participant and to direct the participant to external resources available in the toolkit; (2) at 2 months to coach them for preparation to RTW, or if they have returned to work, and then to coach them in adjusting back to work; and (3) at 3 months to either coach them for preparation to RTW or if they have returned to work and then to coach them in adjusting back to work. The coaching sessions aim to motivate and support workers to use the RTW toolkit, to help them with any activities they might feel stuck with and to discuss their action plan to avoid any relapse. During these sessions, and as part of the process evaluation, the workplace coach will ask about what resources are the worker finding more useful and what are the benefits of using this toolkit.

To reinforce the message of having regular communication with the workplace whilst on sick leave, the worker will have the option to contact the workplace coach (i.e. project researcher) when needed either by email or phone call.

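### The end of follow-up is fixed both from each worker's baseline and from organisation-level randomisation, and a full return that starts in the last 4 weeks cannot be confirmed by month 4

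*Protocol article*

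**What the plan says.** All references are to the Protocol article.

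- **Primary worker measures**, which govern the primary research outcome: "The last data collected will be at 4-month post-randomisation". The same section places randomisation at worksite level.
- **Workers**: "Workers on sick leave will receive the intervention until RTW or 4 months (last follow-up) from when the worker has completed baseline measures".
- **Study design**: "Each of the organisations are the units of randomisation (the clusters"). Each organisation takes part for 12 months. Under **Sample size**, organisations are recruited over 6 months and workers and managers over 18. Under **Allocation to intervention**, a worker takes the arm of the organisation, so there is no individual randomisation date.
- **Table 1** labels month 4 as the end of intervention. Tables 1 and 3 schedule worker measures at baseline, month 2 and month 4.
- **Statistical data analysis**: "Data analysis will be performed after the last trial participant has completed their 4-month post-intervention".
- **Outcome measures**: full return means "working the same days or hours per week as before sickness absence in an identical or equivalent role for at least 4 weeks". Partial return is any hours in any role, with no minimum duration.
- **Objectives** and **Statistical data analysis** define the primary research outcome as days to return to work, whether partial or full.
- **Participant recruitment, inclusion criteria and consent** sets the entry limit at "up to 8 weeks (50 days"). The Abstract has "Workers on long-term sickness absence (LTSA) (between 8 and 50 days").

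**The concern.** Two sections give different end points for the same follow-up, and the one that conflicts with the visit schedule is in the section that governs the primary research outcome. A team applying it as written would stop collecting return dates at a fixed time after the organisation's randomisation. Follow-up length would then depend on when a worker happened to fall ill and enrol. Process outcomes says the pilot will supply the mean and standard deviation for sizing the main trial, and those figures are interpretable only if every worker is observed for the same known period.

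The second issue would remain after the clock is corrected. Full return is defined by a 4-week duration, but observation stops at month 4. No rule says how to label a worker who resumes previous hours shortly before that point. Sustainable return is in the trial's title and aim, so the full/partial label matters.

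**Working it through.** The plan gives no figure of its own to reproduce here. The check is calendar arithmetic with 1 month = 365.25/12 = 30.44 days.

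**1. The two clocks.** Let t be the months from the organisation's randomisation to the worker's baseline (t ≥ 0).

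- Worker-baseline clock (Workers): follow-up = 4 months for every t.
- Randomisation clock (Primary worker measures): follow-up = max(0, 4 − t) months.

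| t (months) | Baseline clock | Randomisation clock |
|---|---|---|
| 0 | 4 | 4 |
| 1 | 4 | 3 |
| 2 | 4 | 2 |
| 3 | 4 | 1 |
| 4 or more | 4 | 0 |

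The clocks agree only at t = 0. Rolling recruitment rules that out for most workers. Table 1 puts worker consent after allocation, and the Employers section has the training video available before workers are recruited.

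**2. Size under the literal randomisation clock.** The documents give no enrolment pattern, so uniform enrolment over L months is an assumption.

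- Share with no follow-up = 1 − 4/L. Mean follow-up over all workers = (4²/2)/L = 8/L months.
- L = 12 (one organisation's involvement): 1 − 4/12 = 67%; mean 8/12 = 0.67 months.
- L = 18 (the whole worker recruitment period): 1 − 4/18 = 78%; mean 8/18 = 0.44 months.
- If every worker enrolled at randomisation, the loss would be 0%. Earlier enrolment moves the figure towards that end.

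**3. The 4-week rule under the worker-baseline clock.**

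- Window: 4 × 30.44 = 121.75 days, about 122.
- Latest start of a full return that can be confirmed: 121.75 − 28 = 93.75, about day 94.
- Share of the window affected: 28/121.75 = 23%.

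This is a share of calendar time, not of workers. The documents give no distribution of return dates.

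**4. Room for a later look at records.** A worker must enrol by month 12 − 4 = 8 to reach month 4 within the organisation's 12-month involvement. Allowing 4 more weeks (28/30.44 = 0.92 months), the limit is 12 − 4 − 0.92, about month 7.1.

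**5. Entry limit.** Eight weeks is 8 × 7 = 56 calendar days or 8 × 5 = 40 working days. Neither is 50. In calendar days, eligibility on days 51 to 56 is undetermined.

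**The case against.** The strongest defence is that the intended clock can be recovered. The Workers section explicitly calls month 4 from worker baseline the last follow-up. Tables 1 and 3 fit only that clock, and the Primary worker measures section itself times the secondary measures from consent. Allocation to intervention also places randomisation after baseline measures, which blurs what the randomisation date means for a worker. This stands: the 67% sizes a literal reading that the schedule does not support and is not a forecast. It does not make the sentence correct, since randomisation still happens once per organisation.

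A reader might infer more from these passages than they support:

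- *A third end of follow-up, at month 8.* The sentence in Statistical data analysis only says when analysis starts. Month 4 is labelled the end of intervention, so it most naturally means the month-4 assessment. It is loosely worded, but it does not set another end of data collection.
- *Late returns are lost from the primary research outcome.* They are not. That outcome counts partial or full return from the first day back, so a late return still has a date. Only its full/partial label is open.
- *Late full returns will be coded as partial.* No passage says so. They are undetermined.
- *A lasting return cannot be told from a one-day attempt.* The monthly text asks whether the worker is still on sick leave and, after a return, whether it is partial or full. The 2- and 4-month surveys ask about current hours, and the employer also records sick-leave days. Relapses between contacts may be missed, but the data do carry some information on duration.

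This is also a feasibility trial with descriptive analysis, and reach, uptake and completion are its primary endpoints. That limits the weight of the point but does not remove it.

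**Conclusion.** The point holds in a limited form. The end-of-follow-up sentence in Primary worker measures contradicts the Workers section and the visit schedule. Applied literally, it would shorten or remove follow-up for later-enrolled workers: 67% with none under uniform enrolment over 12 months, 78% over 18. Both figures rest on that assumption and on the literal reading. On the worker-baseline clock every worker has 4 months.

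Independently of which clock applies, a full return starting after about day 94 of 122 cannot meet its own 4-week definition by month 4. The label is therefore undetermined for starts in the last 23% of the window, while the date of first return remains measured. The two forms of the entry limit are a smaller, separate inconsistency.

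The correction is worth making because it is nearly free and removes a written rule that would produce unequal follow-up.

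**What to change.** 1. In Primary worker measures, end data collection 4 months after each worker's baseline, in place of the post-randomisation wording. In Statistical data analysis, tie the start of analysis to the last participant's 4-month follow-up. Cost: two phrases.
2. State the origin of the return-to-work day count separately, either start of absence or baseline. Workers enter at different points of their absence, so this choice defines the outcome and should not be settled by default when the follow-up clock is corrected.
3. Limit the confirmed full-return label to returns starting at least 4 weeks before the worker's month-4 point. Report later ones as full, not yet confirmed. Cost: one rule and one reporting category.
4. Use organisational records after month 4 to confirm late full returns only where the organisation is still within its 12 months. For the full 4 extra weeks, that means workers enrolled by about month 7. The documents do not say that records are supplied past month 4, so this would need the organisations' agreement and is not costless.
5. Reconcile 8 weeks with 50 days in the eligibility section and the Abstract, and state whether days are calendar or working days.
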